##### Daily Functioning and Mood

OSA impact on daily functioning and mood will be measured through validated versions of the Functional Outcomes of Sleep Questionnaire (FOSQ) [42], Beck Depression Inventory-Fast Screen (BDI-FS) [43], State-Trait Anxiety Inventory (STAI) [44] and *Inventario de Depresión Estado-Rasgo* (IDER) [45]. It has been shown that impaired daytime functioning and depressive and anxiety symptoms are very common in patients with OSA, being higher in patients with more severe OSA and a greater BMI [46]. Hence, participants will complete a set of questionnaires on these symptoms not only to measure inclusion/exclusion criteria but also to analyse potential changes in daily functioning and mood driven by the INTERAPNEA study intervention.

##### Daytime Sleepiness, Sleep Quality and Health-Related Quality of Life

The Epworth Sleepiness Scale (ESS) [47], an 8-item Likert-based scale, will be used to obtain subjective measurements of participant’s daytime sleepiness. Excessive daytime sleepiness is the most common consequence of OSA due to sleep fragmentation and deprivation, and one of the mediating factors for other OSA outcomes such as daily functioning, social and occupational disturbances [6,7,8]. We will also include the Psychomotor Vigilance Test (PVT) [48], regarded as a potential and reliable objective measure of sleepiness, using PC-PVT v 2.0 software (Biotechnology HPC Software Applications Institute [BHSAI], https://pcpvt.bhsai.org/pcpvt/register.xhtml, Frederick, Maryland, USA) on a personal computer [49,50]. This 10 min sustained attention task consists of responding to visual stimulus randomly presented in a black screen each 2 to 10 s, to which participants have to respond by clicking the mouse, with the reaction time being registered and analysed in terms of response speed and number of lapses (reaction time >500 ms).

As sleep quality is also closely related to daily functioning, mood and, thus, participant’s general quality of life and well-being [51,52], we will measure potential benefits of the INTERAPNEA study intervention on these variables through the validated versions of the Pittsburgh Sleep Quality Index (PSQI) [53], Sleep Apnea Quality of Life (SAQLI) [54], Short-Form 36 Health Survey (SF-36) [55], and General Health Questionnaire (GHQ-28) [56].

In addition, we will subjectively measure circadian preference or individual’s chronotype using the validated reduced 5-item version of the Morningness-Eveningness Questionnaire (MEQ) [57], an outcome which has been closely related to age, BMI and, in turn, OSA [58]. Evidence suggests that evening-type chronotype may be highly associated with greater unhealthy eating behaviours, sleep disruption, poor sleep quality and mood disturbances, all playing a part in the development and severity of OSA [58,59].

##### Cost-Effectiveness Analysis Outcome

Cost-effectiveness analysis (CEA) is an essential outcome measurement to be included in RCTs in order to evaluate not only whether a new/alternative intervention produces higher beneficial effects than standard care, but also if those benefits are sufficiently significant to justify the additional costs [60,61,62]. INTERAPNEA will include CEA as an important variable considering the incremental cost-effectiveness ratio (ICER) of the interdisciplinary weight loss and lifestyle intervention related to the usual care (i.e., CPAP). Thus, following standard measures used in medical cost-effectiveness studies and international recommendations [60,61], we will calculate the ratio of the incremental costs and the incremental clinical benefits as the additional expenditure required to generate an additional unit of benefit, expressed as cost per quality-adjusted life-year (QALY) added, and calculated as $CE=\frac{Cost_{2}-Cost_{1}}{QALY_{2}-QALY_{1}}$ [62]. With regard to the cost measurements, we will follow the WHO recommendations for estimating costs contemplated in its CEA guidelines such as the cost of providing the intervention (e.g., labour, capital, and consumables), and costs of accessing the intervention (e.g., resources used and time costs related to seeking or obtaining the intervention) [60]. Furthermore, we will conduct additional sensitivity analyses considering age-weighting as well as weighting of other potential variables such as OSA severity and other secondary outcomes. Apart from calculating the cost-effectiveness ratio of the intervention related to usual care, we will consider the acceptable Spanish cost-effectiveness ratio threshold of 25.000 €–30.000 € per QALY added [63,64]. Subject to the interdisciplinary weight loss and lifestyle intervention resulting in significantly better clinical outcomes and considerably lower costs, the INTERAPNEA intervention could potentially be labelled as a ‘dominant strategy’ [62].

### 2.6. The Intervention Rationale

The design, implementation and evaluation of the INTERAPNEA study intervention components and characteristics are based on results of previous epidemiological and clinical research [1,10] as well as on international evidenced-based clinical practice guidelines for the management of OSA [14,19]. Considering our previous research [1] and with the final aim of the intervention being adaptable to actual primary health-care settings, the intervention will last eight weeks, and will be composed of five different modules: (i) Nutritional behaviour change, (ii) moderate aerobic exercise, (iii) smoking reduction and cessation, (iv) alcohol intake avoidance, and (v) sleep hygiene (see Table 3). Each component will include group-based weekly sessions of 60–90 min lead and supervised by a trained professional in the field (i.e., human nutrition and dietetics, physical activity and sport sciences, and psychology).

The key-factor of this interdisciplinary intervention will be the use of the Transtheoretical Model of Health Behaviour Change (TM) by Prochaska and Diclemente [65]. This well-evidenced model of behaviour change is based on integrating different intervention theories into an interventional approach that considers different stages, processes and principles of change with the premise of establishing sustainable health-related behaviours or habits [65]. Consciousness raising, self-reevaluation, counterconditioning, stimulus control, contingency management, goal-setting, self-monitoring, self-efficacy, and decisional balance are some of the processes and principles of change addressed by this theory and, therefore, included in the five different INTERAPNEA intervention components. Physical and dietary interventions for weight loss using strategies of TM and, thus, psychological support, have been shown to be more effective than other approaches in overweight and obese patients [66] and, specifically, in those with OSA [1].

#### 2.6.1. Nutritional Behaviour Change

Diet quality and dietary patterns have been shown to be closely related to biologic pathways involved in chronic disease etiology [67] and, specifically, to sleep disruption, fragmentation and poor sleep quality found in OSA [68]. Recent studies have shown that high-fat intake is associated with lower sleep efficiency and REM sleep and higher arousal index, whereas high-carbohydrate intake may improve sleep duration and architecture by producing reductions in sleep-onset latency and higher proportions of REM sleep [68]. Regarding intake of micronutrients, vitamin D—which has been associated with insulin resistance in OSA [69]—and magnesium deficiencies have also been related to shorter sleep duration, poorer sleep quality and higher daytime sleepiness [70,71]. Therefore, dietary components including milk, fish, fruit and vegetables may yield beneficial effects on sleep and, in turn, OSA [68].

Furthermore, evidence suggests that sleep disturbances occurring in OSA, in turn, have adverse consequences on calorie intake and expenditure, therefore, exposing a two-way relationship between dietary habits and sleep [72]. Empirical studies have revealed that sleep fragmentation and deprivation are related to higher energy intake of unhealthy foods due to increased hunger, food craving, food reward and portion size selection [73,74,75]. Neurocognitive impairments found in patients with OSA such as attention and episodic memory deficits [76] have also been associated with higher intake of saturated fats, loss of control over food intake, and thus uncontrolled eating [77].

Hence, the INTERAPNEA intervention includes a nutrition module comprising eight 60–90 min sessions (once a week) in a group format addressing dietary patterns using integrated techniques of nutrition education and behavioural change such as specific goal-setting, cognitive restructuring, stimulus control, progressive muscle relaxation, social skills and assertiveness, and problem solving skills. The nutrition education is based on the World Health Organisation’s (WHO) latest recommendations on food intake and healthy diet (see Table 4 for detailed topics) and each session will follow a three-part format: (i) Brief review of previous session and participant’s adherence to recommendations; (ii) development of the main nutrition education components of each session using an interactive group discussion layout; (iii) resolution of participant’s questions and/or concerns, and setting of specific goals. No specific or individualised diet will be indicated to participants.

#### 2.6.2. Physical Exercise

Physical exercise has been shown to be effective in enhancing OSA outcomes and health-related consequences [1,78,79]. Due to the close association between OSA and obesity, a significant and sustainable increase of physical activity could lead to a reduced body weight and, in turn, improvement of the upper airway structure, function, and resting lung volume [12]. Furthermore, physical exercise could also assist the balance of energy intake and expenditure [80], and improve respiratory centre modulation through a reduction of the high leptin and ghrelin hormone levels, which are abnormalities linked to excessive energy intake found in OSA patients [81]. Yet, some research found that exercise benefits on OSA were independent to weight loss [79], suggesting that there are other related mechanisms potentially leading to OSA enhancement such as the increase of sleep efficiency and slow wave sleep [82], and a decrease of fluid accumulation implicated in the upper airway collapse [83], both due to the direct association between physical exercise and sleep.

Therefore, the INTERAPNEA study will include an eight-week physical exercise programme consisting of weekly 60 min sessions of supervised moderated aerobic exercise (i.e., 55–65% of the heart rate reserve) and individualised goal-setting to increase daily steps per week. Previous studies have emphasised that walking may be the exercise modality to achieve higher levels of weight loss and increased cardiorespiratory fitness in adults with obesity and CPAP-treated OSA [84]. Thus, in the weekly supervised training sessions, participants will be required to walk at a moderate intensity for 60 min wearing a heart rate monitor in order to train themselves to walk at that intensity during the week. With respect to goal-setting, they will be advised to increase their daily steps by 15% per week, based on their daily steps logs.

#### 2.6.3. Sleep Hygiene

Sleep hygiene refers to the practice of certain behaviours that facilitate sleep onset and maintenance (e.g., regular sleep schedule, appropriate sleep environment, exercise-training, and healthy nutrition), and avoidance of habits interfering with sleep (e.g., daytime napping, smoking, alcohol intake, and use of hypnotics) [85]. Patients with OSA frequently exhibit poor sleep hygiene including voluntary sleep restriction, irregular sleep schedule, inappropriate sleep environment, and excessive consumption of alcohol, nicotine and/or caffeine [86]. Accordingly, previous studies have supported the inclusion of this component in the treatment of OSA as effective in improving sleep quantity and efficiency, and therefore daytime sleepiness [1,87,88].

The INTERAPNEA study intervention will include a sleep hygiene module comprising 60 min sessions supervised by a psychologist, specialised in the evaluation and treatment of sleep disorders. As most sleep hygiene topics will be covered in simultaneous modules, there will be four sessions distributed over the eight weeks of the intervention, consisting of sleep hygiene education on causes of sleep disturbances and mistaken sleep related knowledge (see Table 5). Sessions will also be based on treating those frequent inadequate sleep habits found in patients with OSA, i.e., sleep restriction, irregular schedule and inappropriate sleep environment.

#### 2.6.4. Reduction and Avoidance of Tobacco Consumption

Smoking has been related to the worsening of OSA via different mechanisms such as changes in sleep architecture and increase of arousal threshold from sleep, reduction of the upper airway muscle tones and neural reflexes, and increased inflammation of the upper airway, all due to nicotine and smoke inhalation [21]. In turn, OSA could also be a predisposing factor for smoking addiction, with nicotine acting as a reward or self-medication for the depressive and anxiety symptoms commonly found in OSA [89]. Although this association has been well elucidated, there is no empirical evidence of the potential beneficial effects of smoking cessation on OSA as, surpringsily, there are no studies focusing on active smoking cessation interventions in patients with this condition [1].

Therefore, we will include a smoking reduction and avoidance module in the INTERAPNEA study intervention. Participants with smoking addiction who are willing to quit will be required to attend a weekly 60–90 min session over eight weeks lead by two clinical psychologists. The specific intervention is based on the group behaviour therapy for smoking cessation by Becoña et al. [90]. This therapy seeks the progressive reduction of tobacco consumption through the use of nicotine and cigarette fading [91], as well as behaviour-change techniques such as information on smoking, self-monitoring, stimulus control, avoidance of withdrawal symptoms, and relapse prevention (see Table 6). Nicotine and cigarette fading has been shown to be the most effective method to reduce and stop smoking with abstinence rates of 86% at the end of treatment and nearly 60% at a 12 month follow-up [92].

Thus, participants will be mainly required to keep a daily record of the number of cigarettes smoked, and triggers for smoking (self-monitoring), change the type of cigarette smoked to a lesser nicotine content brand each week (30%, 60% and 90% nicotine reductions from baseline), reduce the number of cigarettes smoked by 30% weekly, and avoid smoking in three different situations per week (stimulus control). Through the sessions, other behaviour change techniques will be implemented such as discussions on the health consequences of smoking and quitting (motivation), muscle and cognitive relaxation techniques to address withdrawal symptoms, and identification of high-risk situations for smoking and problem-solving skills (relapse prevention).

#### 2.6.5. Reduction and Avoidance of Alcohol Intake

Alcohol intake has also been related to the development and worsening of OSA not only for its direct and indirect effects on weight gain but also due to its negative impact on breathing parameters during sleep [20]. Recent meta-analyses on alcohol and risk of sleep apnoea emphasised that alcohol intake increases the risk of breathing cessation episodes by 25%, thus increasing AHI and reducing mean SaO_2_ during sleep [93]. Potential explanations for these adverse consequences may be the alcohol-related hypotonia of oropharyngeal muscles during sleep, and depression of the arousal response to asphyxia, both caused by the alcohol depressant effects on the central nervous system [94].

Therefore, the INTERAPNEA study intervention will include an alcohol intake reduction and avoidance module supervised by two clinical psychologists. As we will be treating excessive alcohol intake as opposed to alcohol dependence, this module will last eight weeks comprising fortnightly sessions of 60 min. Similar to the smoking cessation module, the main content of this specific component is the progressive reduction of alcohol intake in those participants with no alcohol addiction but excessive consumption (see Table 7). Thus, participants will be indicated to reduce the number of units of alcohol consumed per day/week by 30% each week, keeping a log of alcohol-consumption per day including units of alcohol consumed and triggers of consumption. During the sessions, participants will receive detailed information of alcohol general and specific to OSA health-related consequences. Furthermore, behaviour change techniques such as stimulus control, muscle and cognitive relaxation and problem-solving skills related to alcohol consumption will be used.

### 2.7. Standard Care/Control Group

Participants with moderate-severe OSA randomly assigned to the usual care group (control) will receive, apart from CPAP treatment, general advice on weight loss and lifestyle changes from a sleep disordered-breathing specialist. Informative leaflets describing the positive effects of healthy nutrition, physical activity, sleep hygiene and tobacco and alcohol avoidance for OSA will also be provided to these participants. Additionally, the opportunity to receive the INTERAPNEA study intervention will be offered to this control group after the six month follow-up.

### 2.8. Assessment of Compliance and Integrity of Intervention

Integrity of the intervention and treatment fidelity will be evaluated and ensured including the design and implementation of different strategies of process assessment, monitoring and enhancement in order to guarantee internal and external validity of the trial [95].

Firstly, regarding the study design and provider of intervention training, we developed a comprehensive hand-book for the qualified INTERAPNEA study intervention providers/professionals/training personnel of each module (nutrition, physical exercise, sleep hygiene, and tobacco and alcohol consumption). Each intervention manual identifies the theoretical model of the intervention and provides detailed descriptions of session objectives, treatment guidelines in accordance with each objective (i.e., contents, tasks and activities, recommendations, and timing), participant’s homework, and material needed for each session. We will also provide each participant with an adapted patient-handbook for each intervention component including descriptions of sessions, and work and logging sheets.

Secondly, we will ensure fidelity in the treatment delivery, receipt, and enactment through the use of these intervention protocols/manuals and monitoring of the implementation. Regarding the treatment delivery, the standardisation of the intervention will support the protocol adherence of providers and the treatment differentiation (i.e., the delivery of the target treatment and no other). Furthermore, we will include a check-list for provider’s self-report concerning the achievement of session objectives. With respect to the treatment receipt and enactment, fidelity will be assessed and confirmed through different strategies such as the structuring of the intervention around achievement-based objectives, collecting and reviewing of participants self-monitored data (daily steps log, sleep diaries, alcohol and tobacco consumption records), and information delivery in different formats (e.g., written in the handbooks, and verbal and visual in the sessions).

Finally, apart from the above mention strategies, we will consider complementary approaches in order to reduce participant drop-out rates and increase adherence such as prevention of commitments or vacation periods, use of well-equipped and conditioned facilities, and supervision by a qualified and certified pair of providers in each session, motivating and supporting participants. Participants’ attendance to each intervention session will be recorded by providers, and phone-calls will be made to assess causes of absence and determine further participation in the intervention.

### 2.9. Analytical Approach and Statistical Power/Data Management

We will perform descriptive and exploratory preliminary analyses of all the study variables to reveal violations of statistical assumptions, distributions, imbalances between the study groups, associations between study variables, covariates/confounders, amount of missing data, and drop-out patterns. Covariates or confounders will be secondarily included in the main statistical analysis, evaluating therefore, their impact on the results. To ensure that conclusions are robust, attrition bias will be overcome through intention-to-treat-analysis (ITT), including all participants as originally allocated after randomisation using multiple imputation methods for predicting end-points missing values. Per-protocol comparison of groups, including only those participants who fully completed the originally allocated treatment, will also be computed and compared with ITT analysis results.

The intervention effects on primary and secondary study outcomes will be assessed through multi-level mixed analyses using the package *nlme* [96] from the R statistical program. This method will allow us to analyse differences including time and group allocation as within and between subject factors, respectively, adjusting for potential covariates and levels such as group or set of participants. Therefore, group/condition will be considered as a fixed variable (intervention group compared to control group), and sets/waves of participants as a random factor. With these specifications, we will be able to control the intra-class correlation (per set of participants nested within conditions) between scores at baseline and post-test or follow-up. We will adjust the model including the baseline values of outcomes that are to be analysed in the specific analysis as covariates, as well as other potential covariates such as age, OSA severity, BMI, motivation to change, and attrition propensity. The latter will be calculated using a model predicting the actual attrition with baseline values [97]. Baseline measurements included in these attrition propensity prediction models will include set of participants, participant’s allocation, age, OSA severity, BMI, and motivation to change. The primary and secondary study outcomes that are to be analysed will be those previously mentioned in the outcomes section.

Lastly, we will also estimate standardised effect sizes using Cohen’s d coefficients as the mean difference between the mean change in intervention and control groups from baseline to post-intervention divided by the mean baseline standard deviation [98]: *d* = [((${\bar{X}}_{pre,E}-{\bar{X}}_{pos,E}$) − (${\bar{X}}_{pre,C}-{\bar{X}}_{pos,C}$))/${\bar{S}}_{pre}$].

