### 2.4. Recruitment and Randomisation 

#### 2.4.1. Sample Size

The sample size calculation and power of the study are based on the data of previously reported studies contrasted, combined, and synthesised in our recent systematic review and meta-analysis [1]. We considered following the formula $n=\;\frac{2{\left(Z_{\alpha }\;+\;Z_{1-\beta }\right)}^{2}\sigma^{2}}{\Delta^{2}}$, where *n* is the required sample size, *Z_α_* and *Z*_(1 − *β*)_ are the constants set by convention according to the accepted *α* error and power of the study, respectively, *σ* is the estimated standard deviation, and Δ is the expected effect size. Therefore, we expect to detect an effect size of −8.36 on AHI (pooled raw mean difference of previous trials) [1], considering a type 1 error/α error of 5% (*Z_α_* = 1.64), and a statistical power of 90% (*Z*_(1 − *β)*_ = 1.28). Regarding the estimated AHI variability, we established an *σ* of 11.98, considering the AHI pooled standard deviation of all independent samples included in our previous research [1]. As a result, the expected sample size is ≈35 participants per arm of our controlled clinical trial. However, assuming a maximum of a 17.25% drop-out rate (based on the average drop-out rate of previous studies [1]), we decided to recruit a total sample size of ≈42 participants for each study group. Thus, a total of ≈84 patients with moderate to severe OSA will be enrolled in the INTERAPNEA study. For practical and feasibility reasons, and based on our previous experience [25,26], the study will be conducted in sets of a maximum of 30 persons.

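### The model statement names only set as random, calls it nested in arm although it is crossed, and credits it with controlling within-participant correlation

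*Protocol article*

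**What the plan says.** Section 2.9 of the protocol article says that effects on primary and secondary outcomes "will be assessed through multi-level mixed analyses using the package" nlme in R, "including time and group allocation as within and between subject factors, respectively". The random structure is given in one sentence: "group/condition will be considered as a fixed variable (intervention group compared to control group), and sets/waves of participants as a random factor". The next sentence says what this achieves: "we will be able to control the intra-class correlation (per set of participants nested within conditions) between scores at baseline and post-test or follow-up". On baseline it adds: "We will adjust the model including the baseline values of outcomes that are to be analysed in the specific analysis as covariates". Section 2.9 names no participant-level random effect and no residual correlation over visits.

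Three design facts elsewhere in the article bear on this:

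- Section 2.4.1 gives about 84 men and says that "the study will be conducted in sets of a maximum of 30 persons".
- Section 2.4.4 assigns individual participants by simple, unrestricted randomisation.
- Section 2.5 measures every outcome at weeks 0, 9 and 32.

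**The concern.** Two statements in Section 2.9 are wrong as written.

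**What the set effect does.** A random set effect absorbs whatever makes men in the same wave alike. It says nothing about how closely one man's week-9 score follows his own week-0 score. That correlation needs a participant random effect or a within-participant residual covariance. The article presents the listed terms as enough to control it.

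**Nested or crossed.** Men are randomised individually, so each set contains both arms. Set is therefore crossed with condition.

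In nlme the random and correlation terms have to be written out. An analyst who codes the model from this section could obtain a test of the primary outcome that is anti-conservative, badly conservative or about right, depending on choices the section leaves open. There may also be only about three sets, which is too few to estimate a set variance well.

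**Working it through.** **Inputs from the article.** Difference 8.36 events/h, SD 11.98, Z values 1.64 and 1.28, drop-out 17.25%, about 35 evaluable and 42 recruited per arm (Section 2.4.1); visits at weeks 0, 9 and 32 (Section 2.5).

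**Assumptions, not in the article.** Within-person correlation r from 0.3 to 0.8, equal between all pairs of visits; two-sided 5% tests.

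**The plan's own figure.** n = 2(1.64 + 1.28)² × 11.98² / 8.36² = 35.02 per arm, and 35 / (1 − 0.1725) = 42.3. Both stated sizes reproduce.

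**Nested or crossed.** Under 1:1 simple randomisation, the chance that a set of 28 falls wholly in one arm is 2 × 0.5²⁸ = 7.5 × 10⁻⁹; for a set of 30 it is 1.9 × 10⁻⁹. The number of sets is at least 84 / 30 = 2.8, so 3.

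**Set-only model, three possible contrasts, 35 per arm**

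(a) *Baseline as covariate, arm difference at week 9.* In a simulation (70 men, 3 sets, set SD 2, sets fitted as block effects, 1,500 trials per value of r), the ratio of model SE to true SE was 0.96 to 1.01 and type I error 5-6%. This is essentially correct.

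(b) *Baseline as covariate, one arm effect over weeks 9 and 32.* After baseline adjustment the correlation between the two follow-ups is q = (r − r²)/(1 − r²) = r/(1 + r). Ignoring it makes the SE too small by the factor 1/√(1 + q), and type I error is 2Φ(−1.96/√(1 + q)).

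| r | q | SE ratio | Type I error |
|---|---|---|---|
| 0.3 | 0.231 | 0.90 | 7.7% |
| 0.5 | 0.333 | 0.87 | 9.0% |
| 0.6 | 0.375 | 0.85 | 9.5% |
| 0.7 | 0.412 | 0.84 | 9.9% |
| 0.8 | 0.444 | 0.83 | 10.3% |

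The same simulation gave 8-11% over r from 0.3 to 0.8.

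(c) *Baseline kept as an outcome, week 9 minus baseline by arm.* The true SE is √(4σ²(1 − r)/n). The model that ignores r gives √(4σ²/n) = √(4 × 11.98²/35) = 4.05.

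| r | True SE | Model SE | Ratio | Power, correct model | Power, set-only model |
|---|---|---|---|---|---|
| 0.3 | 3.39 | 4.05 | 1.20 | 69% | 55% |
| 0.5 | 2.86 | 4.05 | 1.41 | 83% | 56% |
| 0.7 | 2.22 | 4.05 | 1.83 | 96-97% | 58% |
| 0.8 | 1.81 | 4.05 | 2.24 | >99% | 59% |

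**Literal nested coding.** Three sets within each of two arms give 6 clusters, and arm is tested between clusters on 6 − 2 = 4 degrees of freedom. The critical t is 2.78 instead of 2.00.

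- *Without baseline adjustment:* the noncentrality is 8.36 / (11.98 × √(2/35)) = 8.36 / 2.864 = 2.92. Power is 60% on 4 df, against 82% on 68 df.
- *With baseline adjustment at r = 0.6:* the noncentrality is 2.92 / √(1 − 0.36) = 3.65. Power is 78%, against 95%.
- *Range with baseline adjustment:* at r = 0.3 the noncentrality is 2.92 / √(1 − 0.09) = 3.06 and power is 64% against 85%. At r = 0.8 it is 2.92 / √(1 − 0.64) = 4.87 and power is 95% against more than 99%.
- *With four sets* (8 − 2 = 6 df): power is 68% unadjusted, and 86% adjusted at r = 0.6.

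**The case against.** The strongest reply is that Section 2.9 describes a multi-level model with time as a within-subject factor, which presupposes a subject level. It also introduces set as one example of a level to adjust for. A condensed article may leave the full covariance statement to the analysis plan. This stands in part: it is not established that repeated scores will be treated as independent. It does not rescue the sentence that credits the listed terms with controlling the correlation over time, because that sentence is a claim about the stated model and it is wrong.

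A reader might go further and infer that the standard error of the primary analysis is wrong. The documents do not support that. The primary contrast is not fixed, baseline is planned as a covariate, and a baseline-adjusted week-9 comparison has an essentially correct standard error even under the set-only model. Where an error does arise, its direction differs between contrasts. Case (c) above also departs from the stated baseline covariate. It is relevant because the same section speaks of correlation between baseline and later scores, as if baseline were also an outcome.

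The nesting phrase has a partial defence. Sessions are delivered in groups (Section 2.6), so intervention men in one set share a real source of correlation. That is a reason to allow for session groups in the intervention arm. It does not make the sets nested in arm.

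Finally, 3 is the minimum number of sets, and the loss to 4 degrees of freedom occurs only under a literal nested coding that the article does not spell out.

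**Conclusion.** The point holds as a misstated model. Set is the only random factor named, it is called nested although randomisation makes it crossed with arm, and it is credited with a correlation it cannot capture.

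The numerical harm is conditional on fitting the terms as written with no participant-level term. It is then nil for a baseline-adjusted week-9 comparison. For a baseline-adjusted effect pooled over both follow-ups, type I error is about 8-10%. For a group-by-time contrast with baseline as an outcome, the standard error is about 1.2 to 2.2 times too large. All of this rests on an assumed within-person correlation of 0.3 to 0.8 with equal correlation between visits. Nested coding with 3 sets would separately cut power to about 60% unadjusted, or about 78% with baseline adjustment at correlation 0.6, against 82% and 95% at 35 per arm.

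The statement should be corrected before analysis because the correction is cheap and the range of outcomes from a literal reading is wide.

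**What to change.** Rewrite the model statement in Section 2.9, or in the analysis plan that governs it, as follows:

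- State a participant random intercept, or a within-participant covariance over visits.
- Enter set as a factor crossed with arm. Make it fixed, since there may be only about three sets.
- Delete the phrase that nests sets in conditions, and the claim that the set factor controls correlation between baseline and later scores.
- State whether baseline is a covariate or one of the outcomes.
- If clustering from group-delivered sessions is to be allowed for, add a session-group effect in the intervention arm as a sensitivity analysis.

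The cost is a changed model statement and about 2 degrees of freedom for set (3 − 1 = 2). No change to the sample, visits or data collection is needed.
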